## Abstract

**Background:**

Gliomas are often associated with symptoms including seizures. Most patients with high-grade gliomas are treated with radiotherapy or radio-chemotherapy. Since irradiation causes inflammation, it may initially aggravate symptoms. Studies focusing on seizure activity during radiotherapy for gliomas are not available. Such knowledge may improve patient monitoring and anti-epileptic treatment. This study evaluates seizure activity during radiotherapy for high-grade gliomas.

**Methods:**

The primary objective this prospective interventional study is the evaluation of seizure activity during a course of radiotherapy for high-grade gliomas. Progression of seizure activity is defined as increased frequency of seizures by > 50%, increased severity of seizures, or initiation/increase by ≥25% of anti-epileptic medication. Seizure frequency up to 6 weeks following radiotherapy and electroencephalography activity typical for epilepsy will also be evaluated. Patients keep a seizure diary during and up to 6 weeks following radiotherapy. Every day, they will document number (and type) of seizures and anti-epileptic medication. Once a week, the findings of the diary are checked and discussed with a neurologist to initiate or adjust anti-epileptic medication, if necessary. Patients complete a questionnaire regarding their satisfaction with the seizure diary. If the dissatisfaction rate is > 40%, the seizure diary will be considered not suitable for the investigated indication. Thirty-five patients (32 patients plus drop-outs) should be enrolled. With this sample size, a one-sample binomial test with a one-sided significance level of 2.5% has a power of 80% to yield statistical significance, if the rate of patients with progression of seizure activity is 30% (rate under the alternative hypothesis), assuming a ‘natural’ background progression-rate of 10% without radiotherapy (null hypothesis).

**Discussion:**

If an increase in seizure activity during a course of radiotherapy for high-grade glioma occurs, the findings of this study may pave the way for a larger prospective trial and will likely lead to closer patient monitoring and better anti-epileptic treatment.

**Trial registration:**

clinicaltrials.gov (NCT04552756); registered on 16th of September, 2020.

## Background

Gliomas represent the most common type of primary brain tumors and are frequently associated with clinical symptoms including seizures [1–7]. The majority of patients with high-grade gliomas (grade III or IV according to the classification of the World Health Organization) receive radiotherapy with or without chemotherapy, either as adjuvant treatment after neurosurgical resection or as definitive treatment after biopsy. Due to an acute inflammatory reaction associated with edema in the irradiated area of the brain and subsequent increase of intracranial pressure, radiotherapy may lead to onset or progression of clinical symptoms including seizures during the course of treatment [8, 9]. To our knowledge, no studies are available that focused on the subacute effect of radiotherapy on seizure activity during a course of radiation treatment in glioma patients. These data would be important to improve monitoring and anti-epileptic treatment of these patients. This study evaluates the seizure activity during radiotherapy for high-grade (grade III or IV) gliomas.

## Methods and design

This single-arm prospective interventional study performed at a single academic center will evaluate the seizure activity during radiotherapy of high-grade gliomas. The study has been approved by the local ethics committee (University of Lübeck, no. 20–311) and registered at clinicaltrials.gov (identifier: NCT04552756).

### Objectives and endpoints

Primary objective is the evaluation of seizure activity during a course of radiotherapy for high-grade gliomas. Progression of seizure activity during the course of radiotherapy compared to baseline is defined as increase of frequency of seizures by more than 50%, increase of severity of seizures (i.e. increase of generalized seizures by more than 50%), or increase of the dose of anti-epileptic medication by at least 25% or initiation of anti-epileptic medication. The latter criterion was defined in accordance with another situation in radiation oncology, radiotherapy of painful bone metastases [10]. These parameters will be assessed using a seizure diary kept by the patients during the course of radiotherapy. In addition, seizure frequency up to 6 weeks following radiotherapy (seizure diary), patient satisfaction with the seizure diary, and electroencephalography (EEG) activity typical for epilepsy will be evaluated.

### Eligibility criteria

Inclusion criteria include histologically proven newly diagnosed or recurrent grade III or IV glioma (associated or not associated with seizures), indication for normo-fractionated radiotherapy, Eastern Cooperative Oncology Group performance score 0–2, age ≥ 18 years, written informed consent (taken by physicians registered as investigators for this trial), and capacity of the patient to cooperate (including the use of a seizure diary). Exclusion criteria include pregnancy/lactation and limited legal capacity or being under legal supervision.

### Assessments

Parameters assessed prior radiotherapy include demographics (age, date of birth, gender), medical history, concomitant diseases, concomitant medication including anti-epileptic treatment, physical examination, histology and grade of glioma, upfront surgery, and planned radiotherapy/radio-chemotherapy.

The following parameters will be assessed during the trial (Fig. 1):
Seizure frequency

**Fig. 1 Fig1:**
[figure not shown]
Timeline of enrolment, interventions and assessments of the SURF-ROGG trial

The patients keep a seizure diary during radiotherapy and up to 6 weeks following radiotherapy. Every day, the patients document the number and type of seizures and intake of anti-epileptic medication. At the end of radiotherapy, the patients are asked to complete a questionnaire regarding their satisfaction with the seizure diary.
2.Objective assessment of seizure activity

To obtain an objective assessment of seizure activity in addition to patient reported outcomes, an EEG is performed during the first and sixth week of radiotherapy, and during the sixth week following radiotherapy.
3.Adverse Events

Adverse events other than seizures will be assessed on an ongoing basis according to CTCAE v5.0 [11].

In addition, potential prognostic factors regarding the increase of seizure activity during the course of radiotherapy will be evaluated including seizure activity at baseline, age, gender, glioma grade, recurrent glioma, isocitrate dehydrogenase (IDH1/2) mutation status, methylation of the O^6^-methylguanine-DNA methyl-transferase (MGMT) gene promoter, tumor site, tumor size, cortical involvement and extent of upfront surgery.

## Interventions

Patients receive the same standard treatment for high-grade glioma as they would have received without participation in this study. If necessary, any care and interventions are permitted during the trial for treatment-related events and other types of comorbidity.

### Glioblastoma (grade IV)

The treatment of glioblastomas includes resection or biopsy of the tumor followed by radiotherapy of the tumor region plus margins. Radiotherapy is performed with a high-precision technique, i.e. volumetric modulated arc therapy (VMAT). Glioblastoma patients with a Karnofsky performance score ≥ 70 and younger than 70 years generally receive normo-fractionated radiotherapy [12]. This applies also to patients aged ≥70 years with methylation of the MGMT gene promoter [12]. The dose-fractionation regimen depends on the proximity of the tumor to structures and organs at risk and is either 30 × 2.0 Gy over 6 weeks or 33 × 1.8 Gy over 6.5 weeks. Tolerance doses of the structures and organs at risk will be considered using the Quantitative Analyses of Normal Tissue Effects in the Clinic (QUANTEC) [13].

Radiotherapy should be combined with temozolomide (TMZ), whenever reasonable. TMZ is given concurrently with radiotherapy plus sequentially following radiotherapy. The dose of concurrent TMZ is 75 mg/m2/day, administered on 7 days per week during the entire course of radiotherapy. Concurrent treatment is followed by 6 courses of sequential TMZ (150–200 mg/m2/day on 5 consecutive days every 4 weeks).

### Anaplastic astrocytoma and anaplastic oligodendroglioma (grade III)

The treatment of grade III gliomas also includes resection or biopsy of the tumor. Postoperative treatment varies between anaplastic astrocytomas and anaplastic oligodendrogliomas. Most patients receive postoperative radiotherapy. Anaplastic astrocytomas with IDH1/2 wild type are generally treated like glioblastomas. If anaplastic astrocytomas show an IDH1/2 mutation, postoperative treatment starts with radiotherapy alone followed by sequential chemotherapy with TMZ (150–200 mg/m2/day on 5 consecutive days every 4 weeks) or 4 courses of PCV including procarbazine (60 mg/m2 on days 8–21), lomustine (110 mg/m2/day on day 1) and vincristine (1.4 mg/m2/day, maximum absolute dose = 2.0 mg, on days 8 and 29, every (6-)8 weeks) [12]. To reduce toxicity, vincristine may be omitted. In case of an IDH1 mutation, astrocytomas and oligodendrogliomas can be differentiated by the 1p/19q co-deletion. Astrocytomas do not have a 1p/19q co-deletion, whereas the co-deletion is present in oligodendrogliomas. Postoperative treatment of anaplastic oligodendrogliomas with IDH mutation and 1p/19q co-deletion starts with radiotherapy alone followed by chemotherapy with 4 courses of PCV [12]. Again, vincristine may be omitted to reduce treatment-related toxicity.

### Seizure diary

The patients keep a seizure diary during the period of radiotherapy and up to 6 weeks following radiotherapy. Every day, the patients document the number and type of seizures and intake of anti-epileptic medication.

Once a week during the radiotherapy course, the seizure diary will be reviewed by a medical staff member. During the 6 weeks following radiotherapy, the patients are contacted by phone (to minimize the number of visits to the hospital) once a week to obtain the information from the seizure diary. During and following radiotherapy, the weekly findings of the seizure diary are discussed with a neurologist to initiate or adjust anti-epileptic medication, if necessary. At the end of radiotherapy, the patients are asked to complete a questionnaire regarding their satisfaction with the seizure diary. In case of a dissatisfaction rate > 40%, the seizure diary will be considered not suitable for patients with high-grade gliomas.

### Electroencephalography (EEG)

The patients receive an EEG during the first and the sixth week of radiotherapy, as well as during the sixth week following radiotherapy. Activity typical for epilepsy includes spike waves, sharp waves and/or sharp slow waves and is classified as absent or present.

## Sample size calculations

The main goal of the study is to generate objective data on the occurrence, frequency and severity of seizures and the use of anti-epileptic medication during the course of radiotherapy applying standardized questionnaires, in order to evaluate the potential effect of radiotherapy in patients with high-grade gliomas and generate hypotheses. Thirty-two patients are required for the statistical analyses. Assuming that 10% of patients do not fulfil these requirements, a total of 35 patients should be enrolled to this trial. With this sample size, a one-sample binomial test with a one-sided significance level of 2.5% has a power of 80% to yield statistical significance if the rate of patients with progression of seizure events during the course of radiotherapy is 30% (rate under the alternative hypothesis), assuming a ‘natural’ background progression-rate of 10% without radiotherapy (null hypothesis). The latter rate was chosen after discussions with experienced neurologists. If the natural course of the disease would lead to a progression-rate of 5% without radiotherapy, the power increases to 98%. Recruitment should be completed within 12 months. The radiotherapy period is 6–6.5 weeks, and follow up is 6 weeks. Thus, duration of the trial is about 15 months.

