## Statistical methods for investigated endpoints

The focus of the statistical analysis is descriptive and exploratory in nature. If statistical tests are applied, they are to be interpreted on an exploratory perspective. All data recorded in the case report forms describing the study population (demographic and clinical characteristics, at baseline) will be analyzed descriptively. Categorical data will be presented in tables with frequencies and percentages. Continuous data will be summarized with at least the following: Frequency (n), median, quartiles, mean, standard deviation (standard error), minimum and maximum. Number of patients with protocol deviations during the study and listings describing the deviations will be provided. The seizure frequency at baseline and during the course of radiotherapy will be calculated by summing the number of seizures in each period and dividing by the total duration (days), excluding days with no available diary data, and multiplying by 7 to normalize to a weekly rate. The resulting normalized frequencies form the basis for calculating the composite primary endpoint. The point estimate of the rate of progressors and the associated 95% confidence interval will be presented. To test whether the rate of progressions is significantly increased beyond 10%, the one-sided binomial test at a one-sided 2.5% significance level will be applied.

Furthermore, a logistic regression model including baseline seizure including seizure activity at baseline, age (≤59 vs. ≥60 years), gender, glioma grade (grade III vs. IV), recurrent glioma (no vs. yes), IDH1/2 mutation status (mutation vs. wild type), methylation of the MGMT gene promoter (yes vs. no), tumor site (frontal vs. temporal vs. parietal vs. other sites), tumor size (≤ median vs. > median), cortical involvement (yes vs. no) and extent of surgery (no resection/biopsy only vs. subtotal resection vs. gross total resection) will be fitted to identify potentially relevant prognostic factors [14].

Adjusted odds ratios and 95% confidence interval (Wald χ2) will be derived. In addition, each component of the primary composite endpoint will be subjected to a separate statistical analysis using the same methods described above. For exploratory purposes, the analyses described above will also be conducted by focusing on the seizures classified as generalized and generalized/grand mal only.

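### The 98% power quoted for a 5% natural progression rate belongs to a test against 5%; the planned test is against 10% and has about 79% power at a 30% rate

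*Protocol article*

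**What the plan says.** The section *Sample size calculations* of the protocol article sets out the design case:

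- Number for analysis: "Thirty-two patients are required for the statistical analyses".
- Test and power: "a one-sample binomial test with a one-sided significance level of 2.5% has a power of 80% to yield statistical significance".
- Rate assumed under radiotherapy: "progression of seizure events during the course of radiotherapy is 30% (rate under the alternative hypothesis").
- Benchmark: "background progression-rate of 10% without radiotherapy (null hypothesis"). The section says that this rate was chosen after talking to experienced neurologists.

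It then adds one variation: "If the natural course of the disease would lead to a progression-rate of 5% without radiotherapy, the power increases to 98" per cent.

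The section *Statistical methods for investigated endpoints* names the test that will be run: "To test whether the rate of progressions is significantly increased beyond 10%, the one-sided binomial test at a one-sided 2.5% significance level will be applied". It gives no test against 5% and no rule under which the null rate would change. It also plans a point estimate of the progressor rate with a 95% confidence interval, and says that any tests are to be read as exploratory.

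**The concern.** The variation makes power depend on the natural course of the disease. The trial has one arm, so the rate without radiotherapy is never observed. It enters the analysis only as the fixed number against which the observed rate is compared, and the methods section sets that number at 10%. If the true natural rate were 5%, neither the benchmark nor the rejection rule would move, and so power would not move either.

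At stake is how a result between the two rejection rules would be read. A reader who thinks 5% is the more realistic background could take the planned test as almost certain to detect a 30% rate, and so give a non-significant result too much weight as evidence against such a rate.

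**Working it through.** **Inputs.** From *Sample size calculations*: n = 32 analysable, one-sided α = 0.025, rate under radiotherapy 0.30, null rate 0.10, alternative natural rate 0.05. From *Statistical methods for investigated endpoints*: the planned null rate, 0.10.

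**Method.** Exact one-sample binomial test. The critical count r is the smallest integer with P(X ≥ r | n, p0) ≤ 0.025. Power is P(X ≥ r | n, 0.30).

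**Step 1: reproduce the 80%.** With n = 32 and p0 = 0.10:

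- P(X ≥ 7 | 0.10) = 0.0358, which is above 0.025.
- P(X ≥ 8 | 0.10) = 0.0117, so r = 8.
- Power = P(X ≥ 8 | 0.30) = 0.788.

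This agrees with the stated 80% to ordinary rounding.

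**Step 2: reproduce the 98%.** With n = 32 and p0 = 0.05:

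- P(X ≥ 4 | 0.05) = 0.0738, which is above 0.025.
- P(X ≥ 5 | 0.05) = 0.0204, so r = 5.
- Power = P(X ≥ 5 | 0.30) = 0.981.

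This agrees with the stated 98%. The figure is therefore the power of a test with a 5% null.

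**Step 3: the planned test when the natural rate is 5%.** The null stays at 10%, r stays at 8 and the rate under radiotherapy stays at 30%. The natural rate appears nowhere in P(X ≥ 8 | 32, 0.30), so power is again 0.788.

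| | Null 10% (planned) | Null 5% (not planned) |
|---|---|---|
| Reject at | 8 or more of 32 | 5 or more of 32 |
| Actual one-sided size | 0.0117 | 0.0204 |
| Power at 30% | 78.8% | 98.1% |

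**Step 4: where the gap comes from.** The two rules disagree at 5, 6 or 7 progressors, that is 5/32 = 16% to 7/32 = 22%. At a true rate of 30%, P(5 ≤ X ≤ 7) = 0.193, which is the whole difference: 98.1% − 78.8% = 19.3 percentage points.

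**Step 5: the rules are not interchangeable.** If the natural rate is 10%, as the design assumes, and radiotherapy adds nothing, the rule of 5 or more would reject with probability P(X ≥ 5 | 32, 0.10) = 0.211, against the nominal 0.025. The 98% cannot be claimed for the planned analysis by treating the 5% benchmark as available alongside it.

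**The case against.** The strongest defence is that the sentence is a design sensitivity. The section has just identified the natural rate with the null hypothesis, so asking what happens at a natural rate of 5% can mean asking what happens with a 5% null. On that reading the arithmetic is right, as step 2 shows. This explains the origin of the figure, and it means that 98% is not a miscalculation. It does not rescue the sentence as written: the text says that power increases, straight after giving the power of the 10% test, and does not say that the null, and with it the test, would have to change.

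A second defence is the planned 95% confidence interval. If it is exact (an assumption, since the method is not named), its lower limit is 5.3% at 5 of 32 and 3.5% at 4 of 32. The interval would then exclude 5% at 5 or more progressors, the very rule with 98.1% power. So a comparison with 5% could be read from a planned output. This stands and softens the consequence, as does the declared exploratory status of testing. It remains true that the only named test of the progression rate is against 10%.

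A reader might also infer that the other sample size figures are wrong. The documents do not support that. Exact power of 78.8% fits a stated 80%. On enrolment, the protocol says "Assuming that 10% of patients do not fulfil these requirements, a total of 35 patients should be enrolled to this trial". Strict inflation gives 32/0.9 = 35.6, hence 36, so 35 is at most one patient low. It still leaves 32 after three losses (3/35 = 8.6%, close to the assumed 10%).

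Nor should one go further and argue that a lower background would reduce power because the rate under radiotherapy would fall with it. The protocol fixes that rate at 30% and does not assume a constant increase over background.

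**Conclusion.** The point holds for the 98% sentence alone. The figure is the power of a test that the plan does not contain. For the planned test against 10%, power at a 30% rate with 32 evaluable patients is 78.8% whatever the natural rate, so the test misses such a rate about one time in five (21.2%), not one time in fifty.

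This rests on the exact binomial test, 32 evaluable patients, a 30% rate under radiotherapy, and a null that stays at 10% as the methods section states. The design, the sample size and the planned analysis are not called into question. The error is in a stated operating characteristic, and its practical weight is moderate because inference is exploratory and the interval will be shown.

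**What to change.** In *Sample size calculations*, delete the sentence on the 5% natural rate, or replace it with wording such as: *A power of 98% would apply only if the null rate were set to 5%; the planned test against 10% has an exact power of about 79% at a 30% rate with 32 evaluable patients, whatever the natural rate.*

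The cost is wording only. No patient number, threshold or analysis changes; the stated figure becomes less favourable.

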## Statistical methods for investigated endpoints

The focus of the statistical analysis is descriptive and exploratory in nature. If statistical tests are applied, they are to be interpreted on an exploratory perspective. All data recorded in the case report forms describing the study population (demographic and clinical characteristics, at baseline) will be analyzed descriptively. Categorical data will be presented in tables with frequencies and percentages. Continuous data will be summarized with at least the following: Frequency (n), median, quartiles, mean, standard deviation (standard error), minimum and maximum. Number of patients with protocol deviations during the study and listings describing the deviations will be provided. The seizure frequency at baseline and during the course of radiotherapy will be calculated by summing the number of seizures in each period and dividing by the total duration (days), excluding days with no available diary data, and multiplying by 7 to normalize to a weekly rate. The resulting normalized frequencies form the basis for calculating the composite primary endpoint. The point estimate of the rate of progressors and the associated 95% confidence interval will be presented. To test whether the rate of progressions is significantly increased beyond 10%, the one-sided binomial test at a one-sided 2.5% significance level will be applied.

Furthermore, a logistic regression model including baseline seizure including seizure activity at baseline, age (≤59 vs. ≥60 years), gender, glioma grade (grade III vs. IV), recurrent glioma (no vs. yes), IDH1/2 mutation status (mutation vs. wild type), methylation of the MGMT gene promoter (yes vs. no), tumor site (frontal vs. temporal vs. parietal vs. other sites), tumor size (≤ median vs. > median), cortical involvement (yes vs. no) and extent of surgery (no resection/biopsy only vs. subtotal resection vs. gross total resection) will be fitted to identify potentially relevant prognostic factors [14].

Adjusted odds ratios and 95% confidence interval (Wald χ2) will be derived. In addition, each component of the primary composite endpoint will be subjected to a separate statistical analysis using the same methods described above. For exploratory purposes, the analyses described above will also be conducted by focusing on the seizures classified as generalized and generalized/grand mal only.

In order to describe the time profiles of seizure frequencies in more detail, normalized seizure frequencies over time will be calculated within 3-week intervals, namely weeks 1–3 and 4–6 during radiotherapy, and weeks 1–3 (7–9 in total) and 4–6 (10–12 in total) following radiotherapy. These frequencies will be subjected to descriptive statistics as well as graphical presentations by means of box-and whisker diagrams. For exploratory purposes, the Wilcoxon signed-rank test will be applied to compare the two-time windows during the course of radiotherapy; the Friedman-Test will be applied to assess whether there is any difference in seizure frequencies between all of the time intervals during the course of radiotherapy and thereafter.

In addition, the percent change from baseline in seizure frequency will be considered and subjected to descriptive analysis. For further exploratory analysis, the rates of patients experiencing any seizure (yes/no) at baseline and at each time interval will be estimated together with their associated confidence intervals. Subsequent analyses focus on the clinically relevant generalized seizures only.

Patient satisfaction with the seizure diary will be assessed at the end of radiotherapy using a questionnaire and subjected to descriptive analysis. In case of a dissatisfaction rate > 40%, the seizure diary will be considered not suitable for patients with high-grade gliomas. EEG activity typical for epilepsy will be performed during the first and sixth week of radiotherapy, and the sixth week following radiotherapy. EEG activity typical for epilepsy is classified as absent or present. Statistical analysis is focused on data description only. A mean change to baseline (during first week of radiotherapy) by 50% regarding the number of patients with EEG activity typical for epilepsy will be considered clinically relevant.

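### The baseline seizure rate in the primary endpoint is calculated from diary days, but the diary is described only from the start of radiotherapy, and no pre-radiotherapy seizure count or window is stated

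*Protocol article*

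**What the plan says.** All references are to the protocol article.

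- **Objectives and endpoints** defines the primary endpoint as a change: "Progression of seizure activity during the course of radiotherapy compared to baseline is defined as increase of frequency of seizures by more than 50" per cent, or a rise in generalized seizures by more than 50%, or a dose increase of at least 25% or start of anti-epileptic medication. On the data source it says: "These parameters will be assessed using a seizure diary kept by the patients during the course of radiotherapy".
- **Statistical methods for investigated endpoints** gives one formula for both periods: "The seizure frequency at baseline and during the course of radiotherapy will be calculated by summing the number of seizures in each period". Each sum is then turned into a rate per day of observation, under this rule: "excluding days with no available diary data, and multiplying by 7 to normalize to a weekly rate". It adds: "The resulting normalized frequencies form the basis for calculating the composite primary endpoint".
- **Seizure diary** gives the diary period: "The patients keep a seizure diary during the period of radiotherapy and up to 6 weeks following radiotherapy". The Abstract, the text with Fig. 1 and the Discussion give the same period.
- **Assessments** lists what is collected beforehand: "Parameters assessed prior radiotherapy include demographics (age, date of birth, gender), medical history, concomitant diseases, concomitant medication including anti-epileptic treatment", followed by examination, histology, surgery and planned treatment. No number or type of seizures and no look-back window is listed.
- The only baseline window stated anywhere is for EEG: "A mean change to baseline (during first week of radiotherapy) by 50% regarding the number of patients with EEG activity typical for epilepsy".

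**The concern.** The formula for the baseline rate needs diary days before radiotherapy, and the diary descriptions provide none. This is more than a detail left to a fuller document: two statements in the article do not fit together, and they meet in the primary endpoint. A later analysis plan can choose a definition, but it cannot create diary days that were not collected.

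The frequency and generalized-seizure components both depend on this baseline. So do the percent change from baseline, the proportion with any seizure at baseline, and baseline seizure activity as a factor in the logistic model. The trial has one arm and tests the progressor rate against a fixed 10%, so no control group would absorb an artefact from the way baseline is measured.

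**Working it through.** **1. Does any reading of the text give a usable baseline?**

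| Reading | Fit with the text |
|---|---|
| Diary days before radiotherapy | The formula needs them; no description of the diary includes them |
| Medical history taken before radiotherapy | Possible, but there are no diary days to divide by, no window is given, and the source differs from the daily diary |
| First week of radiotherapy, as for EEG | Same diary, but stated for EEG only. It would lie inside the treatment period and overlap the weeks 1–3 interval, and the text lists baseline separately from the intervals |

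None works without changing a statement. For medication the position is better, because anti-epileptic treatment before radiotherapy is on the assessment list.

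**2. The plan's own test.** Inputs from Sample size calculations: 32 evaluable patients, null rate 10%, alternative 30%, one-sided 2.5%. Exact binomial, X ~ Bin(32, p):

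- P(X ≥ 7 | 0.10) = 0.036, too large; P(X ≥ 8 | 0.10) = 0.012. Significance therefore needs at least 8 progressors.
- P(X ≥ 8 | 0.30) = 0.788, in line with the stated 80%.
- For a null of 5% the cut-off is 5, and P(X ≥ 5 | 0.30) = 0.981, in line with the stated 98%.

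The sample size is not in dispute.

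**3. How much the window matters for one patient.** These are assumptions, not figures from the article: a patient with ongoing seizures, Poisson counts at an unchanged rate λ per week, complete recording, 6 weeks of radiotherapy, a baseline of w weeks, and any seizure after a zero baseline counted as progression. With baseline count X ~ Poisson(λw) and on-treatment count Y ~ Poisson(6λ), the false-progression chance is P(Y/6 > 1.5·X/w).

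| λ per week | w = 1 | w = 2 | w = 4 | w = 6 |
|---|---|---|---|---|
| 0.5 | 0.577 | 0.418 | 0.341 | 0.294 |
| of which zero baseline | 0.576 | 0.350 | 0.129 | 0.047 |
| 1 | 0.398 | 0.352 | 0.289 | 0.233 |

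The zero-baseline share is e^(−λw) × (1 − e^(−6λ)). At λ = 0.5 and w = 1 this is 0.6065 × 0.9502 = 0.576. At λ = 1 and w = 1 it is 0.3679 × 0.9975 = 0.367 of 0.398. The 1-week figures are therefore mostly a zero-baseline effect, and the article does not say how such patients are classified.

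**4. Dilution at trial level.** Patients without seizures are eligible. The Discussion gives a pre-radiotherapy seizure prevalence of 21.5% (grade IV) and 48.8% (grade III) from the group's own study. As an illustration, let 21.5% have ongoing seizures at 0.5 per week. The contribution to the overall progressor rate is then 0.215 × 0.577 = 12%, 0.215 × 0.418 = 9%, 0.215 × 0.341 = 7% and 0.215 × 0.294 = 6% for the four windows.

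**5. What a shifted background rate does to the test.** With the cut-off of 8 out of 32 and no radiotherapy effect:

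| True background rate | P(X ≥ 8) |
|---|---|
| 10% | 0.012 |
| 12% | 0.032 |
| 15% | 0.096 |

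Two percentage points in the background rate are enough to exceed the nominal 0.025.

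**The case against.** The strongest reply is that an article condenses a fuller protocol. The assessment list is introduced as inclusive, Fig. 1 is not shown, and the analysis uses baseline seizure activity as a factor, so some baseline seizure data are evidently intended. That stands in part. A reader might infer that the trial never records baseline seizures, and the documents do not support that. They support only that the text states no source or window, and that the formula does not fit the diary period.

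A reader might also infer that baseline will come from recall, that recall misses seizures, and that the endpoint therefore leans towards progression. No text says baseline is recalled, and the direction of any bias has no source in the article. Both remain assumptions.

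Nor should the 58% be read as the effect of the window alone, or as a trial-level rate. It is almost entirely a zero-baseline effect and applies only to patients with ongoing seizures. Moving from 4 to 6 weeks at the same rate changes 34% only to 29%. Chance variation around a 50% threshold would remain under any definition.

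Finally, the article calls its analysis descriptive and exploratory. That tempers the consequence, but the binomial test at 2.5% is still the stated test of the primary endpoint and depends on this baseline.

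**Conclusion.** The point holds as an internal contradiction. The baseline rate for the frequency and generalized-seizure components is defined on diary days that the described diary does not cover, and no other pre-radiotherapy seizure count is stated. The medication component is less affected.

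Under the stated Poisson assumptions, the per-patient chance of apparent progression without any change runs from 58% to 29% at 0.5 seizures per week, and from 40% to 23% at 1 per week, as the baseline lengthens from 1 to 6 weeks. The trial-level effect is smaller and depends on how many patients have ongoing seizures. The test has little room for it: a background rate of 12% or 15% gives a false-positive chance of 3.2% or 9.6%. This should be settled before enrolment, because prospective baseline data cannot be collected once radiotherapy has begun.

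**What to change.** - Hand out the existing diary at consent.
- Record on the case report form the number and type of seizures in one fixed pre-radiotherapy window, for example 4 weeks.
- In Statistical methods for investigated endpoints, define that window and its source as the baseline, and bring Objectives and endpoints, Assessments (with the text at Fig. 1) and Seizure diary into line with it.
- State how a patient with a zero baseline is classified, for all seizures and for generalized seizures.
- Add a sensitivity analysis restricted to prospectively recorded baseline days.

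The cost is a change of wording, one added form item and earlier issue of a diary that already exists; treatment is untouched. The downside is that the prospective baseline will be short for patients who start radiotherapy quickly, and any recalled part of the window keeps its recall error.
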